### Objectives

Primary objective: To determine the safe and tolerable dose of NTP in patients with breast cancer.
Primary endpoint: Using a 3 + 3 dose escalation design up to a maximum dose of 3, a safe and tolerable dose of NTP in patients with breast cancer will be determined. The adverse effects of NTP produced by the CPJ will be assessed based on DLTs, AEs, physical exams, quality of life (QOL) questionnaires, and clinically significant changes in laboratory evaluations. The AEs will use the descriptions and grading scales found in the revised NCI Common Terminology Criteria for Adverse Events (CTCAE). This study will utilize CTCAE Version 5.0 for adverse event reporting. All patients that receive the treatment and complete the 1-week follow-up visit will be evaluated for acute toxicity. All patients who receive the treatment and complete the 3-month follow-up visit will be evaluated for long-term events.
Secondary objectives: To assess the safety and tolerability of NTP in patients with breast cancer and to assess the cosmetic effects of NTP treatment in patients with breast cancer.
Secondary endpoints: Number of patients with adverse events linked to NTP treatment and type of adverse event and number of patients with cosmetic alterations linked to NTP treatment and type of alteration. The adverse events of special interest (AESIs) will be assessed through QOL questionnaires (questions on breast appearance and texture) and through photo collection. The following AESIs will be recorded throughout the study:
Fatigue; grade 3,Breast pain; grade 3,Skin ulceration; grade 3,Chest wall necrosis; grade 3,Breast atrophy; grade 3,Change in breast texture,Cosmetic issues,Discoloration.

Exploratory objective: To assess the impact of NTP treatment on cancerous and normal tissues.
Exploratory endpoint: Evidence of cancer cell death and absence of normal tissue degradation in samples treated with NTP ex vivo or in situ. The exploratory objective (to assess the impact of NTP treatment on cancerous and normal tissues) will be assessed through the analysis of treated and untreated tissues.

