### Rationale for the starting dose and dosing schedule

The dose of NTP produced by the CPJ is described by the duration (min) of the treatment. Based on the in vivo studies performed with the CPJ V4.4, the maximum dose used will be 5 min of treatment at 13 W (0 Hz, 100% DC), 5000 sccm helium and 25 sccm O_2_ per 7 mm^2^. This dose has proven to be efficacious and safe in mice (*manuscript in preparation*). For V5 (clinical version) of the CPJ, by comparing the physical, electrical and thermal properties of V4.4 and V5, the equivalent conditions were found to be 220 V, 100 Hz, 80% DC, 5000 sccm helium and 20 sccm O_2_ in the capillary, with stationary treatment for 5 min per 7 mm^2^. This dose will be defined as the highest dose assessed in this trial, dose 3 (Table 1). The dose will not be increased above this mark in search of the maximum tolerated dose (MTD), as it would not necessarily be associated with improved treatment efficacy (probably due to the increase in temperature that accompanies the increase in applied power). Instead, the maximum dose used in this study will be the dose that has been found to be efficacious (i.e., dose 3) in vivo or lower in the presence of dose-limiting toxicities (DLTs). A DLT is defined as any of the following attributable to NTP administration (definitely, probably, or possibly) occurring after NTP administration until the 1-week post-op follow-up visit:

Fever; grade 4,Breast infection; grade 4,Skin ulceration; grade 4,Chest wall necrosis, grade 4.

**Table 1 Tab1:** Doses used in the breast cancer PAINT first-in-human investigation

Dose Level #	Dose	Group
**Dose Level − 1**	**2 min per 7 mm** ^**2**^	**Group C – if 1 DLT out of 3 or 2 DLTs out of 6 (30 min max)**
Dose Level 1 (starting dose)	3 min per 7 mm^2^	Group C, Cohort 1 (30 min max)
Dose Level 2	4 min per 7 mm^2^	Group C, Cohort 2 (30 min max)
Dose Level 3	5 min per 7 mm^2^	Group C, Cohort 3 (30 min max) Group A (15 min max) Group B (15 min max)

Three dose levels will be assessed for DLTs. If DLT toxicity occurs in the initial cohort for group C, then a provision has been added for a fourth lower dose to be explored with an expanded patient cohort (in bold text)

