### Treatment plan

The minimum number of patients required to complete this first-in-human study will be 9, and the maximum sample size for the study will be 30. At the end of each group/cohort, a safety cohort review will be performed to analyze the safety data and approve the transition to the next group/cohort if applicable.

The study will be conducted at the CHUM site in Montreal, Quebec.

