#### Group C (*n* = 6–24)

After safety is confirmed for group B, group C patients will be enrolled based on the 3 + 3 dose escalation rule up to a maximum dose level of 3 (Table 1). Even if the safety of dose 3 is confirmed in group B, the first patient cohort treated in group C will receive a lower starting dose of 3 min per 7 mm^2^ (dose 1) (Table 1). In cohort 1, at dose level 1, the first patient will be enrolled and treated with NTP. After follow-up #2 one-week post-op, only if there was no DLT in the first patient could accrual be reopened to enroll the second and third patients in the cohort. Subjects will be enrolled in cohorts of three each. If no DLT is encountered in any of the 3 subjects after 1-week post-op, dose escalation according to Fig. 2 will be allowed. If one of the 3 subjects experiences a DLT, three additional subjects will be enrolled at the same dose level, and if none of these 3 additional subjects experience a DLT, dose escalation will be allowed. A safety cohort review will be conducted after the patients in each cohort complete the 1-week post-op follow-up visit. The MTD will be defined as the next lower dose level below the one in which > 1/3 of the subjects or ≥ 2/6 of the subjects experience DLT. Up to 6 additional subjects may be enrolled at the MTD to obtain additional data on the safety and efficacy of the product. If escalation to dose level 3 is reached and < 1 out of 6 subjects experience DLT, dose escalation will stop, and 6 additional subjects will be enrolled at dose level 3 to obtain additional data on the safety and efficacy of the product.

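### For one DLT in the first three Group C patients at dose level 1 (first patient clear), Table 1 opens dose level −1, while the Group C text enrols three more at the same level and may then escalate

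*Protocol article*

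**What the plan says.** Four places in the protocol article bear on a DLT at the starting dose of Group C (dose level 1, 3 min per 7 mm²).

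- **Table 1, row for dose level −1** (2 min per 7 mm²): the level is used in Group C "if 1 DLT out of 3 or 2 DLTs out of 6".
- **Table 1, footnote:** "If DLT toxicity occurs in the initial cohort for group C, then a provision has been added for a fourth lower dose". The initial Group C cohort is cohort 1, at dose level 1.
- **Group C section, expansion and escalation:** "If one of the 3 subjects experiences a DLT, three additional subjects will be enrolled at the same dose level". The section then sets the condition for moving up once that expansion is complete: "if none of these 3 additional subjects experience a DLT, dose escalation will be allowed".
- **Group C section, MTD:** "The MTD will be defined as the next lower dose level below the one in which" more than 1/3, or at least 2/6, of the patients have a DLT.

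The Group C section also has a sentinel rule for cohort 1. Patients 2 and 3 can be enrolled only if patient 1 has had no DLT by the one-week visit. It states no further step at level 1 if patient 1 does have one.

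**The concern.** The 3 + 3 rule produces the primary endpoint: under Objectives, it is the means by which "a safe and tolerable dose of NTP in patients with breast cancer will be determined". After each cohort, the safety cohort review has to "approve the transition to the next group/cohort if applicable". If one of the first three patients at level 1 has a DLT, that review would hold two printed instructions for the same data. One goes down to 2 min per 7 mm². The other stays at 3 min and may go on to 4 min. Either action departs from a printed rule.

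What is at stake is mainly lost escalation. If Table 1 is followed, dose level 3 may never be tested in tissue that stays in the patient. Groups A and B receive dose 3, but all their treated tissue is removed.

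**Working it through.** **1. The rules side by side, for exactly 1 DLT in the first 3 at level 1 and patient 1 clear**

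| Source | Action |
|---|---|
| Table 1, first trigger | Open level −1 |
| Table 1 footnote | Provides for level −1, with no higher threshold |
| Group C section | Three more at level 1; escalate if 0 of those 3 have a DLT |

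The sentinel rule does not remove the conflict, because a clear patient 1 reopens accrual and the single DLT is then in patient 2 or 3.

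**2. Which rule is intended**

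- The MTD rule treats a level as too toxic above 1/3, or from 2/6. Exactly 1 of 3 does not exceed 1/3. Table 1 has the same two fractions without the inequality signs.
- Table 1's second trigger, 2 of 6, needs six patients at level 1 in the escalation phase. If any 1 of 3 already leads down, level 1 is left after three patients whatever the result: up after 0/3, down otherwise.
- The Group C maximum of 24 is only consistent with the text rule: three levels of six plus six expansion patients give 6 + 6 + 6 + 6 = 24, and 24 + 3 + 3 = 30 matches "the maximum sample size for the study will be 30". With Table 1's first trigger, level 1 could be passed only at 0/3, giving 3 + 6 + 6 + 6 = 21, or 27 in all. But four levels of six also give 24, so the ceiling settles nothing.

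**3. How often it matters**

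The article gives no DLT rate. DLTs are four grade 4 events, so low rates p are assumed, with q = 1 − p and independent patients.

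- Conflict: patient 1 clear (q) and exactly one DLT in the next two (2pq), so 2pq².
- Escalation from level 1, given patient 1 clear. Text: q² + 2pq · q³ = q² + 2pq⁴. Table 1: q².
- Loss from following Table 1: 2pq⁴.

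| p | Conflict, 2pq² | Escalate, text | Escalate, Table 1 | Loss (points) |
|---|---|---|---|---|
| 1% | 2 × 0.01 × 0.9801 = 2.0% | 99.9% | 98.0% | 1.9 |
| 2% | 2 × 0.02 × 0.9604 = 3.8% | 99.7% | 96.0% | 3.7 |
| 5% | 2 × 0.05 × 0.9025 = 9.0% | 98.4% | 90.3% | 8.1 |

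The escalation figures assume no return to level 1 after level −1; the article provides for none.

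**4. A DLT in patient 1**

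This has probability p: 1%, 2% or 5%. The Group C text does not reopen accrual at level 1, so its expansion step cannot start. The Table 1 trigger and footnote are the only printed route onward. A correction that merely raised both to two or more DLTs would leave this case with no stated action.

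**The case against.** The best defence is that the sentinel rule lets both Table 1 triggers work. A DLT in patient 1 leads to level −1; a DLT in patient 2 or 3 leads to expansion, and 2 of 6 then leads to level −1. The MTD rule says when a level is above the MTD, not when the lower dose opens. The footnote is permissive and sides with Table 1. Fig. 2, which holds the acceptance criteria for Group C, is not shown and may say which rule governs. The safety cohort review must approve each transition in any case.

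Part of this stands. Table 1 and its footnote do carry the response to a DLT in patient 1, and the correction must keep it. The evidence on intent is an indication, not proof. The rest does not remove the conflict. Table 1 says 1 out of 3, not a DLT in the first patient, when only one patient has been treated. Fig. 2 may show the preferred rule but cannot make both printed statements true. A review committee needs one threshold to apply.

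A reader might also infer that the conflict puts patients at risk or leaves the primary endpoint undetermined. The article supports neither. Following Table 1 means a lower dose, and the dosing rationale already accepts a final dose below level 3 when DLTs occur.

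**Conclusion.** The contradiction is real and needs no assumption: for 1 DLT in 3 at level 1 with patient 1 clear, the article prints two incompatible actions. The too-toxic threshold and the 2 of 6 trigger favour the Group C text, so the Table 1 trigger is the one to correct.

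The effect is modest. At the assumed rates of 1% to 5% the conflict arises in 2.0% to 9.0% of trials, and following Table 1 costs 1.9 to 8.1 percentage points of escalation from level 1, given a clear first patient. Higher DLT rates would raise the frequency at first, but the article gives no ground for choosing one. The correction is still worthwhile, because this rule decides the dose and a single DLT in a cohort is the very event it exists to govern.

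**What to change.** In Table 1, change the trigger for dose level −1 to: *≥2 DLTs out of 3 or ≥2 DLTs out of 6, or a DLT in the first (sentinel) patient of cohort 1*. Make the footnote say the same, so that a sentinel DLT keeps a stated route. Check Fig. 2 against the result.

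No patients are added. With six at level 1, six at level −1 and six in expansion, the level −1 route needs at most 6 + 6 + 6 = 18 in Group C; after a sentinel DLT it needs at most 1 + 6 + 6 = 13. The maxima of 24 for Group C and 30 for the study stand. The cost is an edit to one table row and its footnote, plus the check of Fig. 2.

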### Treatment plan

The minimum number of patients required to complete this first-in-human study will be 9, and the maximum sample size for the study will be 30. At the end of each group/cohort, a safety cohort review will be performed to analyze the safety data and approve the transition to the next group/cohort if applicable.

The study will be conducted at the CHUM site in Montreal, Quebec.

#### Group A (*n* = 3)

All three subjects can be enrolled concurrently. These patients will be treated concomitantly as the treatment will take place ex vivo. Once three subjects are enrolled in group A, it will be closed to enrollment. The enrollment of group B patients can start immediately (Fig. 1).

**Fig. 1 Fig1:**
[figure not shown]
Study schema. BC = breast cancer. Simplified representation of the proceedings of the breast cancer PAINT study

Treatment of part of the tumor and tumor bed ex vivo will be performed at dose 3 (5 min per 7 mm^2^) for a maximum of 15 min (i.e., treatment of 21 mm^2^). During surgery, the tumor and the tumor bed will be removed. Part of the tumor and tumor bed will be reserved for NTP treatment, while the rest will be sent to pathology as part of the standard of care (SOC) procedures. All tissues exposed to NTP will be analyzed.

#### Group B (*n* = 3)

Three patients in group B will then be enrolled concurrently and treated with NTP, also concomitantly, as none of the NTP-treated tissues will be left inside the patients. Group B will then be closed to enrollment until safety assessment of all three subjects is performed at post-op follow-up #2. Safety will be confirmed if none of the three patients experience DLTs (Fig. 1).NTP treatment of part of the tumor bed in situ at dose level 3 (5 min per 7 mm^2^) for a maximum of 15 min (i.e., treatment of 21 mm^2^). During surgery, part of the tumor bed will be treated with NTP inside the patient. The treated tumor bed will be removed from the patient immediately after NTP treatment and analyzed as part of this clinical protocol. Part of the tumor removed during surgery will be sent to the PW laboratory for treatment with NTP at dose 3 and analysis as part of this clinical protocol. The rest of the tumor and tumor bed will be sent to pathology as part of the SOC procedures. No treated tissue will stay inside the patient.

#### Group C (*n* = 6–24)

After safety is confirmed for group B, group C patients will be enrolled based on the 3 + 3 dose escalation rule up to a maximum dose level of 3 (Table 1). Even if the safety of dose 3 is confirmed in group B, the first patient cohort treated in group C will receive a lower starting dose of 3 min per 7 mm^2^ (dose 1) (Table 1). In cohort 1, at dose level 1, the first patient will be enrolled and treated with NTP. After follow-up #2 one-week post-op, only if there was no DLT in the first patient could accrual be reopened to enroll the second and third patients in the cohort. Subjects will be enrolled in cohorts of three each. If no DLT is encountered in any of the 3 subjects after 1-week post-op, dose escalation according to Fig. 2 will be allowed. If one of the 3 subjects experiences a DLT, three additional subjects will be enrolled at the same dose level, and if none of these 3 additional subjects experience a DLT, dose escalation will be allowed. A safety cohort review will be conducted after the patients in each cohort complete the 1-week post-op follow-up visit. The MTD will be defined as the next lower dose level below the one in which > 1/3 of the subjects or ≥ 2/6 of the subjects experience DLT. Up to 6 additional subjects may be enrolled at the MTD to obtain additional data on the safety and efficacy of the product. If escalation to dose level 3 is reached and < 1 out of 6 subjects experience DLT, dose escalation will stop, and 6 additional subjects will be enrolled at dose level 3 to obtain additional data on the safety and efficacy of the product.

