### Statistical analysis

The following study populations are defined and will be analyzed as specified below. The population evaluable for safety will be the safety population.

The Intent to Treat population: 24 patients.

Safety population: up to 30 patients.

Per protocol population: any patient who received plasma treatment within group C.

The study population will consist of all patients who are registered and who received one dose of NTP. All analyses will be conducted using the study population. Any patient who is registered for this trial but never receives study treatment will be described, including the reason(s) for nonparticipation.

Subject characteristics will be described in a table comprising age, tumor type and grade, and Eastern Cooperative Oncology Group (ECOG) status. Subjects will be summarized using their group/cohort.

Summary statistics will be used to describe baseline characteristics and other outcomes of interest. Categorical endpoints will be summarized using proportions and frequencies. Continuous endpoints will be summarized using the mean, median, range or standard deviation. Subgroup summarization based on dose level or other criteria may also be conducted.

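### When a dose level fails, the level below becomes the MTD with no minimum number treated and only optional expansion, so the declared dose can rest on 0 DLTs in 3 patients

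*Protocol article*

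**What the plan says.** All the rules are in the protocol article, Group C (n = 6–24).

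- Escalation: "If no DLT is encountered in any of the 3 subjects after 1-week post-op, dose escalation according to Fig. 2 will be allowed". A level with no DLT is thus left after 3 patients.
- A level grows to 6 only after one DLT: "If one of the 3 subjects experiences a DLT, three additional subjects will be enrolled at the same dose level".
- MTD: "The MTD will be defined as the next lower dose level below the one in which > 1/3 of the subjects" have a DLT, or at least 2 of 6 do. No minimum number treated at that lower level is given.
- Expansion after a failed level: "Up to 6 additional subjects may be enrolled at the MTD to obtain additional data on the safety and efficacy of the product".
- Expansion when level 3 is reached without failure: "dose escalation will stop, and 6 additional subjects will be enrolled at dose level 3".

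The two expansions serve the same stated purpose, more safety and efficacy data, but one is permitted and the other required. The result feeds the primary endpoint in the Objectives section, under which "a safe and tolerable dose of NTP in patients with breast cancer will be determined".

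**The concern.** The protocol asks for less evidence in the situation that calls for more. If no level fails, the final dose has at least 9 patients (3 + 6). If level 2 or 3 fails, the dose one step down is declared, and nothing obliges the investigators to treat more than the 3 patients it may already have. Toxicity has then just been seen one step higher, and three event-free patients say little about the declared dose.

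At stake is the support for the primary conclusion, and for the dose carried into the phase II trial that the Discussion foresees if this study succeeds.

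**Working it through.** **Inputs.** The escalation, MTD and expansion rules are those of the Group C section. The protocol gives no target DLT rate, confidence level or expected DLT rates. I assume exact one-sided 95% limits and a range of DLT rates.

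**1. The stated Group C size.** A level uses 3 patients (0/3, or at least 2 DLTs in the first 3) or 6 (1 DLT in the first 3).
- Maximum: 6 + 6 + 6 + 6 (expansion) = 24, as stated.
- Minimum: 3 + 3 = 6, as stated. Only two completed paths give it: level 1 shows 0/3 and level 2 fails within 3; or level 1 fails within 3 and level −1 shows 0/3. In both, a dose is declared on 3 patients with no expansion. The stated minimum thus includes the path at issue.

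**2. What the counts exclude.** For 0 events in n, the upper limit is 1 − 0.05^(1/n).
- 0/3: 1 − 0.368 = 63.2%
- 0/6: 1 − 0.607 = 39.3%
- 0/9: 1 − 0.717 = 28.3%

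For 1/6, the other count on which a level can pass, solving (1 − p)^6 + 6p(1 − p)^5 = 0.05 gives 58.2%. These limits depend only on the counts and the confidence level.

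A level with a true DLT rate of 30%, 40% or 50% shows 0/3 with probability (1 − p)^3 = 34.3%, 21.6% or 12.5%.

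**3. How often the MTD has only 3 patients before any expansion.** For a level with DLT rate p:
- z = (1 − p)^3 is the chance of 0/3
- P = z + 3p(1 − p)^5 is the chance of passing
- F = 1 − P is the chance of failing

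Then:
- MTD at level 1 or 2 through failure of the next level: P1·F2 + P1·P2·F3
- the same, resting on 0/3: z1·F2 + P1·z2·F3

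Example at 5/10/20%: z1 = 0.857, z2 = 0.729, P1 = 0.973, P2 = 0.906, F2 = 0.094, F3 = 0.291.
- Any such MTD: 0.091 + 0.257 = 0.348
- Resting on 0/3: 0.080 + 0.207 = 0.287
- Share: 0.287 / 0.348 = 82%

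| Assumed DLT rates, levels 1/2/3 | MTD set by failure of level 2 or 3 | of all trials: MTD on 0/3 | share on 0/3 |
|---|---|---|---|
| 1/2/5% | 3.1% | 2.9% | 95% |
| 2/5/10% | 11.7% | 10.5% | 90% |
| 5/10/20% | 34.8% | 28.7% | 82% |
| 10/20/30% | 58.9% | 44.7% | 76% |
| 10/20/40% | 70.7% | 53.3% | 75% |
| 10/25/40% | 73.8% | 55.6% | 75% |
| 20/30/40% | 60.0% | 42.7% | 71% |
| 30/40/50% | 46.8% | 32.5% | 70% |

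The overall frequency runs from about 3% to 56%. The share stays within about 70–95%.

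**4. Size if the rule is tightened, on paths where level 2 or 3 fails.**
- Six always added: from 3 + 3 + 6 = 12 to 6 + 6 + 6 + 6 = 24.
- Six in total required: from 3 + 3 + 3 = 9 to 6 + 6 + 6 = 18.

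**The case against.** - **Optional expansion is ordinary in a 3 + 3 design, and the stated minimum of 6 suggests a deliberate choice.** The second part is fair: the rule agrees with the stated size, so this is a design weakness and not an arithmetical slip. But the protocol itself makes expansion compulsory at level 3 for the same purpose and gives no reason for the difference.
- **Fig. 2 is not visible and may set a minimum.** That stands as a limit, so the point is made on the text shown.
- **The dose is not judged on DLTs alone.** The Objectives section also lists adverse events, examinations, questionnaires and laboratory changes, and a safety review follows each cohort. A reader might infer that the plan treats no DLT in 3 as proof of safety; it does not say so. The other assessments would still come from the same 3 patients.
- **Severe toxicity may be rare.** DLTs are grade 4 events only, and the article reports no severe events in earlier plasma studies. At low rates the situation is uncommon, about 3% at 1/2/5%, so no single overall probability should be the headline.
- **Group B adds data.** Those patients receive dose level 3 on 21 mm² rather than 42 mm², with all treated tissue removed. They say little about a lower level where most treated tissue stays.

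Two stronger readings lack support. Because "Categorical endpoints will be summarized using proportions and frequencies", a reader might infer that the plan wrongly omits confidence limits; an analysis plan commonly supplies these, and it is not shown. A reader might also take 2 of 6 as a DLT rate of 33% that the plan calls too toxic; it is a boundary on observed counts, and no target rate is stated.

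**Conclusion.** The point holds as a statement of what the rule permits. After failure of level 2 or 3, the declared dose can rest on 0 DLTs in 3 patients, with an exact one-sided 95% upper limit of 63%. The size of the gap does not depend on assumed rates; how often it arises does.

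It does not arise when level 3 passes, and the MTD may instead rest on 1/6. If level 1 fails, the note to Table 1 promises an expanded cohort at level −1 without a size, while the MTD definition would name that level before anyone is treated there. Those passages must be reconciled.

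This is a worthwhile and inexpensive improvement, not a flaw that invalidates the design. An analysis plan could not repair it, because it concerns how many patients are enrolled.

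**What to change.** Make the six-patient expansion at the MTD compulsory, as for level 3. A lighter version is to require 6 patients in total at a level before it is declared the MTD. If expansion stays optional, state that an MTD resting on 3 patients is provisional; this needs no extra patients.

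With either enrolment change, the protocol should also say how DLTs among the added patients bear on the declared dose. Otherwise the extra data need not affect the conclusion.

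Cost:
- The Group C maximum stays at 24, but up to 6 already budgeted patients become compulsory when level 2 or 3 fails.
- The Group C minimum of 6, given in the Abstract and in the Group C section, must be restated: on those paths at least 12 if six are always added, or 9 if six in total are required. The path through level −1 still allows 6 unless its cohort size is fixed too.
- The total minimum in the Treatment plan must be restated as well. It is given as 9, although 3 + 3 + 6 = 12 already under the present rule; the stated maximum does agree (3 + 3 + 24 = 30).

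### The stopping rule at dose level 3 (fewer than 1 DLT in 6) leaves 1/6 without a next step, although 1/6 is accepted at levels 1 and 2

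*Protocol article*

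**What the plan says.** All the decision rules are in the protocol article, Treatment plan, Group C. No DLT in the first three patients at a level permits escalation. For a single DLT the rule is "If one of the 3 subjects experiences a DLT, three additional subjects will be enrolled at the same dose level". A clean second set of three then opens the next level: "and if none of these 3 additional subjects experience a DLT, dose escalation will be allowed". The MTD is the level below the one at which "> 1/3 of the subjects or ≥ 2/6 of the subjects experience DLT", and "Up to 6 additional subjects may be enrolled at the MTD to obtain additional data on the safety and efficacy of the product". The top level has its own sentence: "If escalation to dose level 3 is reached and < 1 out of 6 subjects experience DLT, dose escalation will stop", followed by six further patients at level 3.

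The primary endpoint in Objectives is that, by 3 + 3 escalation up to dose 3, "a safe and tolerable dose of NTP in patients with breast cancer will be determined". The section on the rationale for the starting dose makes dose 3 the ceiling, "or lower in the presence of dose-limiting toxicities (DLTs", and gives no count of DLTs. It also sets the event: "A DLT is defined as any of the following attributable to NTP administration", followed by four grade 4 events (fever, breast infection, skin ulceration, chest wall necrosis) counted up to the one-week visit.

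**The concern.** The threshold at level 3 does not fit the steps that lead to it. Under those steps six patients are treated at a level only after a DLT has been seen, so a rule asking for fewer than 1 in 6 describes a result that cannot occur before the expansion. A clean 0/3 satisfies it only if the threshold is read as a rate. That part is a wording fault, since dose 3 is plainly the answer after 0/3.

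The substantive gap is 1/6. At levels 1 and 2 it counts as tolerated and the trial moves up. At level 3 it fails the rule for stopping and expanding, falls short of the rule for declaring a level too toxic, and cannot lead to escalation because no higher level exists. The sentence that closes the dose search for the primary endpoint is therefore silent on a result that the design can produce. What stays open is whether dose 3 is the recommended dose and whether six more patients receive it in a first-in-human study in which most of the treated tissue is left in place.

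**Working it through.** **1. Possible results at one level.** Three patients are treated, and three more only after exactly one DLT. The end states are 0/3, 2/3, 3/3, 1/6, 2/6, 3/6 and 4/6. 0/6 is not among them.

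**2. Printed consequence at level 3.**

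| Result at level 3 | Fewer than 1 in 6? | More than 1/3, or at least 2/6? | Next step in the text |
|---|---|---|---|
| 0/3 | yes, as a rate | no | stop; 6 more at level 3 |
| 2/3, 3/3 | no | yes | level 2 is the MTD; up to 6 more there |
| 2/6, 3/6, 4/6 | no | yes | level 2 is the MTD; up to 6 more there |
| 1/6 | no | no | none |

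**3. The plan's own size.** The stated Group C range of 6–24 reproduces. The smallest path is 3 + 3 = 6, for example level 1 passing with 0/3, level 2 failing in three patients and no optional expansion. The maximum of 24 arises when levels 1 and 2 each take six, level 3 fails in six, and six more are treated at level 2: 6 + 6 + 6 + 6 = 24. Accepting 1/6 at level 3 also gives 6 + 6 + 6 + 6 = 24. With the printed threshold, the longest path that accepts level 3 is 6 + 6 + 3 + 6 = 21. Since 24 is reached either way, the sample size does not show which threshold was meant.

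**4. How often 1/6 would occur.** The article gives no DLT rate, so p is assumed, the same at every level and independent between patients.

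- Once level 3 is reached: P(1/6) = 3p(1−p)² × (1−p)³ = 3p(1−p)⁵. At p = 5%: 0.15 × 0.7738 = 0.116.
- Passing level 2: s = (1−p)³ + 3p(1−p)⁵.
- Passing level 1, where a DLT in the first patient is taken to stop accrual: s₁ = (1−p)³ + 2p(1−p)⁵.
- From the start of Group C: s₁ × s × P(1/6). At p = 5%: 0.935 × 0.973 × 0.116 = 0.106.

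| Assumed p | 1/6, once level 3 is reached | 1/6 at level 3, from the start of Group C |
|---|---|---|
| 0.5% | 1.5% | 1.5% |
| 1% | 2.9% | 2.8% |
| 2% | 5.4% | 5.3% |
| 5% | 11.6% | 10.6% |
| 10% | 17.7% | 13.6% |

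If one of the first three at level 3 has a DLT, the chance of ending at 1/6 is (1−p)³: 97% at p = 1%, 86% at 5% and 73% at 10%. At these rates it is the usual outcome of that situation.

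Table 1 gives a different trigger for dose level −1 (1 DLT in 3). That is a separate conflict at level 1. If it governed, the last column would be slightly lower; the gap at level 3 would remain.

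**5. What hangs on the missing step.** When 1/6 occurs, Group C has treated between 3 + 3 + 6 = 12 and 6 + 6 + 6 = 18 patients. It ends there without the expansion, or at 18 to 24 with it. The one-sided 95% exact (Clopper–Pearson) upper bound on the DLT rate at dose 3 is 58% for 1/6. It would be 34% for 1/12, that is, if none of the six added patients had a DLT.

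**The case against.** The strongest reply is that this is one badly worded sentence. Fig. 2, which is not shown, is captioned as giving the acceptance criteria for each cohort and may state the right one. A safety cohort review follows each cohort and would see a 1/6 result. The declared dose would almost certainly be 3, the literal text exposes fewer patients rather than more, and grade 4 attributable events within a week are likely to be rare. The sentence might also be read as filling level 3 to six patients before expanding, which makes 0/6 reachable. Finally, a stricter trigger at the top dose could be deliberate, given the remark about going lower if DLTs appear.

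Much of this limits the size of the problem, and the probabilities above reflect that. It does not remove it. A different criterion in Fig. 2 would contradict the sentence, which would still need correcting. The review is described without a rule for this result. Filling level 3 to six first still leaves 1/6 without a step. If a stricter rule at level 3 was intended, the text would have to say what follows 1/6, and it does not. The 34% against 58% contrast is indeed the favourable case, because it assumes six further patients without a DLT.

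**Conclusion.** The point holds and should be fixed. As printed, the level-3 threshold does not match the plan's own acceptance of 1/6 or its rule of at least 2/6 for rejecting a level, and 1/6 at level 3 has no stated consequence. This follows from the rules alone and does not depend on any assumed rate. The practical size does: from the start of Group C the case arises with probability 1.5% to 5.3% for p of 0.5% to 2%, and 10.6% to 13.6% for p of 5% to 10%, with the lower range more plausible for grade 4 events. When it arises, the text leaves open 6 or 12 patients at dose 3 and does not state the recommended dose, although dose 3 is the natural reading. The conclusion is limited to the printed text, since Fig. 2 could not be seen.

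**What to change.** Replace the level-3 sentence with wording to this effect:

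> At dose level 3, if 0 of the first 3 patients, or no more than 1 of the first 6, has a DLT, escalation ends, dose level 3 is the recommended dose, and 6 further patients are treated at that level. If 2 or more of the first 3 to 6 patients have a DLT, dose level 2 is the MTD.

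Bring Fig. 2 into line if it differs. The cost is one sentence, with no new rule for the expansion patients. Group C keeps its maximum on both paths: 6 + 6 + 6 + 6 = 24 if level 3 passes, and 6 + 6 + 6 plus up to 6 at level 2 = 24 if it fails. The one real consequence is that, compared with the literal text, a 1/6 result would mean six more patients treated at dose 3. If the sponsor does not want that after a grade 4 event, the sentence should instead state the dose declared after 1/6 and that no expansion follows.
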